# Ultrasound-guided breast-sparing surgery to improve cosmetic outcomes and quality of life. A prospective multicentre randomised controlled clinical trial comparing ultrasound-guided surgery to traditional palpation-guided surgery (COBALT trial)

**DOI:** 10.1186/1471-2482-11-8

**Published:** 2011-03-16

## Abstract

**Background:**

Breast-conserving surgery for breast cancer was developed as a method to preserve healthy breast tissue, thereby improving cosmetic outcomes. Thus far, the primary aim of breast-conserving surgery has been the achievement of tumour-free resection margins and prevention of local recurrence, whereas the cosmetic outcome has been considered less important. Large studies have reported poor cosmetic outcomes in 20-40% of patients after breast-conserving surgery, with the volume of the resected breast tissue being the major determinant. There is clear evidence for the efficacy of ultrasonography in the resection of nonpalpable tumours. Surgical resection of palpable breast cancer is performed with guidance by intra-operative palpation. These palpation-guided excisions often result in an unnecessarily wide resection of adjacent healthy breast tissue, while the rate of tumour-involved resection margins is still high. It is hypothesised that the use of intra-operative ultrasonography in the excision of palpable breast cancer will improve the ability to spare healthy breast tissue while maintaining or even improving the oncological margin status. The aim of this study is to compare ultrasound-guided surgery for palpable tumours with the standard palpation-guided surgery in terms of the extent of healthy breast tissue resection, the percentage of tumour-free margins, cosmetic outcomes and quality of life.

**Methods/design:**

In this prospective multicentre randomised controlled clinical trial, 120 women who have been diagnosed with palpable early-stage (T1-2N0-1) primary invasive breast cancer and deemed suitable for breast-conserving surgery will be randomised between ultrasound-guided surgery and palpation-guided surgery. With this sample size, an expected 20% reduction of resected breast tissue and an 18% difference in tumour-free margins can be detected with a power of 80%. Secondary endpoints include cosmetic outcomes and quality of life. The rationale, study design and planned analyses are described.

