Although BCT is considered the least invasive surgical method for treatment of breast cancer, cosmetic outcomes vary widely. Studies have reported satisfactory cosmetic results in only 60-80% of patients, with cosmetic failure rates up to 40%. Factors determining cosmetic outcome after BCT include the volume of resected breast tissue, the amount of radiotherapy, the site of the tumour in the breast, the type of incision and postoperative complications such as wound infection. Overall, a large volume of resected breast tissue is the major determinant of a poor cosmetic outcome. Regardless of the size of the breast, excision volumes exceeding 85 cm^3 ^result in a 50% rate of cosmetic failures, whereas smaller excision volumes result in only a 22% rate of cosmetic failures. Therefore, surgeons should excise the tumour with only a small volume of surrounding breast tissue [10-15].

As a practical and reasonable guideline during surgery, the aim is to achieve a safe and cosmetically acceptable resection margin of 5-10 mm. It should be noted that the size of the tumour-free resection margin (> 1 mm) is unrelated to local recurrence or overall survival. Higher risks of local recurrence have been shown only with evident involvement of the tumour on the inked resection margins. Therefore, there is no need to excise a tumour with a large volume of adjacent breast tissue. This is also stated by the Dutch national guidelines. Accurate excision leads to a smaller and more precise volume of surrounding breast tissue removal without compromising the minimal tumour-free margin [16-19].

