### Sample size calculation

The sample size was calculated based on the primary endpoint: volume of resected breast tissue. Previous studies have shown that excision volumes exceeding 85 cm^3 ^result in significantly higher cosmetic failure rates. In our recent retrospective multicentre study it was found that in 33.9% (244/726) of the patients the excision volumes exceeded 85 cm^3^. In 98.8% (241/244) of these patients, the CRR was > 1.0, implying that excess tissue was excised [20]. It can therefore be concluded that, in 33.2% (241/726) of all patients, excessive tissue resection resulted in impairment of the cosmetic outcome. Assuming that this excessive resection can be avoided with US-guided surgery, it is expected that only 10% of women will have excessive breast tissue resection (a ratio of > 1.0) that results in a worse cosmetic outcome (resection volume > 85 cm^3^). Therefore, we assume a difference in resected volume of 22.3% in favour of the US group. With a statistical power of 80% to detect this 22.3% improvement as significant (P < 0.05), we will require 57 patients in the palpation group and 57 patients in the US group. The margin status is currently involved in 22.5% of palpable breast tumour excisions. To improve this rate to 5%, we will require 60 patients in the palpation group and 60 patients in the US group. Therefore, the target sample size will be 120 patients.

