## Discussion and Conclusion

The goals of breast-conserving surgery are to obtain adequate margins and good cosmetic results. Both goals are poorly defined, and there is no universal acceptable standard. According to Dutch national guidelines, a negative margin is defined as a margin of ≥ 1 mm of normal tissue intervening between the tumour and the edge of the specimen. Resections are described as focally involved when cancer cells invade the resection margin in a maximum of two microscopic slides or when margins include < 1 mm of normal tissue. The margins are described as involved or positive when microscopic cancer cells are situated on the inked resection border. It has been well-established that the status of the margin affects the local recurrence rate. Therefore, re-excision is indicated for involved margins. Vrieling et al. showed that patients with focally involved margins have lower rates of recurrence when treated with a higher radiation boost dose, equal to patients with adequate margins. Therefore, a higher boost dose is given to patients with focally involved margins without further surgery. This has been confirmed by national guidelines [15-19].

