- avoiding a higher boost dose for focally involved margins

- avoiding re-excision or even mastectomy for involved margins

Approximately 9000 out of 13000 breast cancer patients are diagnosed with a palpable breast cancer in the Netherlands each year, and around 5000 patients undergo breast-conserving surgery for a palpable breast cancer. An improvement of cosmetic outcomes in an estimated n = 1115 (22.3%) of all patients treated with breast-conserving surgery can be achieved by USS. Also, an estimated n = 875 (17.5%) less operations will be necessary after treatment by US-guided surgery (A re-operation costs about € 7 000, -, so eventually € 6 125 000, - might be saved by this method each year).

In conclusion, this randomised controlled trial aims to demonstrate the superiority of USS versus PGS for the treatment of patients with palpable breast cancer in terms of the sparing of breast tissue, oncological margin status, cosmetic outcomes and quality of life.

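### The stated 80% power for a 20% cut in resected volume follows from no stated input: the trial was sized on the proportion of patients above 85 cm³

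*Protocol article*

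**What the plan says.** The Sample size calculation section opens with the endpoint: "The sample size was calculated based on the primary endpoint: volume of resected breast tissue". The next steps concern a different quantity. From the sponsor's retrospective series it takes that "in 33.2% (241/726) of all patients, excessive tissue resection resulted in impairment of the cosmetic outcome", meaning resection above 85 cm³ with a ratio above 1.0. Under ultrasound guidance "it is expected that only 10% of women will have excessive breast tissue resection (a ratio of > 1.0") with a volume above 85 cm³. The section then concludes: "Therefore, we assume a difference in resected volume of 22.3% in favour of the US group". It requires 57 per group for 80% power at P < 0.05. A separate margin calculation (22.5% against 5%) raises this to 60 per group, 120 in total.

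The abstract condenses this to "an expected 20% reduction of resected breast tissue and an 18% difference in tumour-free margins can be detected with a power of 80"%.

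The Discussion and Conclusion reuses the same percentage as patient benefit: "An improvement of cosmetic outcomes in an estimated n = 1115 (22.3%) of all patients treated with breast-conserving surgery can be achieved by USS". It also projects 875 fewer operations a year and a saving of €6,125,000.

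Two other statements bear on those projections. The Background says that volumes above 85 cm³ "result in a 50% rate of cosmetic failures, whereas smaller excision volumes result in only a 22% rate of cosmetic failures". The Discussion says that "a higher boost dose is given to patients with focally involved margins without further surgery".

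**The concern.** A fall in the share of patients above a cut-off, a percentage fall in mean volume and a fall in the rate of cosmetic failure are three different effects. The article uses nearly the same number for all three. The sample size rests on the first, the abstract reports power for the second, and the Discussion claims the third.

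The primary endpoint is affected. The Statistical analysis section plans a t-test for continuous variables and a chi-square test for dichotomous ones, and does not say which one carries the primary comparison. A reader who relies on the abstract would take a volume result short of a 20% reduction as coming from a trial designed with 80% power to detect it. Nothing in the article establishes that. The yearly benefit and savings figures also go further than the article's own rates allow.

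**Working it through.** **1. Reproduce the 57 per group.** Inputs from the Sample size calculation section: p1 = 241/726 = 0.332, p2 = 0.10, alpha 0.05, power 80%. Sidedness is not stated; two-sided is assumed. With p̄ = 0.216:

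n = [1.96·√(2·p̄(1−p̄)) + 0.842·√(p1(1−p1) + p2(1−p2))]² / (p1−p2)² = 48.2

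With the continuity correction, n′ = (n/4)·[1 + √(1 + 4/(n·0.232))]² = 56.5, rounded up to **57**. This matches exactly.

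The gap is 33.2 − 10 = **23.2** points, not 22.3. A true 22.3-point gap would need 61 per group (32.3% vs 10%) or 62 (33.2% vs 10.9%) by the same formula. So 57 belongs to 23.2 points, and 22.3 is a slip, probably transposed digits.

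**2. Margins.** 22.5% vs 5% without continuity correction gives 59.6, so **60** per group, with 80.3% power. The gap of 17.5 points is the abstract's 18% after rounding. This half of the power sentence is sound.

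**3. Power for the sized proportion at 60 per group.** 33.2% vs 10% gives **88%** (uncorrected).

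**4. The abstract's 20% read as percentage points.** 33.2% vs 13.2% at 60 per group gives **74%** power; 69 per group are needed (79 with the correction).

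**5. The abstract's 20% read as a cut in volume.** This needs an SD, and none is given. Assume lognormal volumes with coefficient of variation CV, so that the SD of log volume is s = √ln(1 + CV²) and the standardised effect is d = −ln(0.8)/s = 0.223/s. Two-sample t-test on log volume, 60 per group:

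| CV (assumed) | s | d | Power |
|---|---|---|---|
| 0.3 | 0.294 | 0.760 | 98% |
| 0.4 | 0.385 | 0.579 | 88% |
| 0.5 | 0.472 | 0.472 | 73% |
| 0.7 | 0.631 | 0.353 | 48% |
| 1.0 | 0.833 | 0.268 | 31% |

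The difference detectable with 80% power at 60 per group is 0.516 SD. This needs s ≤ 0.223/0.516 = 0.433, so CV ≤ √(exp(0.433²) − 1) = **0.45**. On the untransformed scale the limit is a CV of about 0.39.

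**6. Volume change implied by the sized effect.** Under the same model, going from 33.2% to 10% above 85 cm³ is a shift of 1.282 − 0.434 = 0.847 SD of log volume. The volume cut is 1 − exp(−0.847·s): 28% at CV 0.4 and 51% at CV 1.0. So 20% is not a paraphrase of the planned effect over that range. At CV 0.3 the two come close (22%).

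**7. Cosmetic projection.** The article's figure is 0.223 × 5000 = 1115. By the Background's rates, moving a patient below 85 cm³ changes the failure probability by 50% − 22% = 28 points:
- with the printed 22.3: 0.223 × 0.28 = 6.2%, or **312** of 5000
- with the correct 23.2: 0.232 × 0.28 = 6.5%, or **325** of 5000

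**8. Re-operation projection.** 0.175 × 5000 = 875, and 875 × €7,000 = €6,125,000. The Background defines the 22.5% as focally positive or positive margins. The Discussion says that focally involved margins do not lead to further surgery. The split is not given, so a corrected count cannot be derived from the article.

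**The case against.** The strongest reply is that nothing is lost in practice. The target of 120 comes from the margin calculation, which reproduces, and the proportion has about 88% power at that size. At the effect actually planned, a volume analysis would do even better: under the lognormal model the 0.847 SD shift gives a t-test on log volume over 99% power. All of this stands, and it rules out three stronger readings.

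First, a reader might infer that the trial is underpowered for volume. The article does not show this. The low figures come from assumed CVs of 0.7 and 1.0; at 0.4 or below, log-scale power for a 20% cut exceeds 80%.

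Second, a reader might infer that cosmetic outcome is presented as adequately powered. It is not. The abstract's power sentence covers tissue and margins, and the next sentence lists cosmetic outcome as secondary. The closing sentence of the Discussion states superiority on cosmetic outcome as an aim, with no power figure. The Statistical analysis section already plans 95% confidence intervals for the differences.

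Third, it is tempting to replace 1115 with 325. That figure counts only failures avoided through volume and applies the Background's rates as if they were causal. The Discussion names margin status as a second route to cosmetic benefit.

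The national projections are also closing remarks that affect neither the endpoint nor the sample size. What the reply does not answer is the power sentence itself, which attaches 80% to an effect that was never calculated.

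**Conclusion.** The point holds as a wrong statement of what was powered. The 57 per group belongs to a 23.2-point difference in a proportion. The 22.3% difference in resected volume and the 20% reduction with 80% power do not follow from any stated input.

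How far off the 80% is cannot be settled from the article. It is about 74% if 20 points were meant. If a volume reduction was meant, it lies anywhere from 98% to 31% for CVs of 0.3 to 1.0, under an assumed lognormal distribution and a log-scale t-test.

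The 1115 figure is about 3.5 times what the article's own failure rates give through volume alone (1115/312 = 3.6; 1115/325 = 3.4). The 875 operations and the savings are overstated to the extent that focally involved margins make up the 22.5%.

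**What to change.** 1. In the abstract and the Sample size calculation section, state the powered effect as a reduction from 33.2% to 10% (23.2 points) in the proportion with resection above 85 cm³ and a ratio above 1.0. Name that proportion and its test as the sized primary comparison.
2. Alternatively, keep volume as the primary variable, name its test, and restate the detectable difference (about 0.52 SD at 60 per group) using the SD from the sponsor's 726-patient series.
3. Correct 22.3 to 23.2 wherever it is used.
4. In the Discussion, remove or qualify the 1115. If a figure is kept, say that the volume route alone gives about 6% of patients (312 to 325 of 5000) by the Background's rates.
5. Qualify the 875 operations and the €6,125,000, since the 22.5% includes focally positive margins that the article says are not re-operated.

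The cost is wording, plus one recalculation from data the sponsor already holds if option 2 is chosen. The stated figures become less favourable. No extra patients are needed.

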**Conclusion:**

The COBALT trial is a prospective, multicentre, randomised controlled study to assess the efficacy of ultrasound-guided breast-conserving surgery in patients with palpable early-stage primary invasive breast cancer in terms of the sparing of breast tissue, oncological margin status, cosmetic outcomes and quality of life.

**Trial Registration Number:**

Netherlands Trial Register (NTR): NTR2579

## Background

Breast cancer is the most common cancer among women in the western world. It affects women of all ages and the lifetime risk of developing invasive breast cancer is 12-13%. The 5-year disease-free survival rate for node-negative breast cancer, however, is excellent (98%). Breast cancer surgery has changed dramatically over the past few decades. Breast-conserving therapy (BCT) was introduced in the 1970s and refers to the surgical removal of the breast tumour in all cases followed by radiotherapy to eradicate residual tumour cells. The introduction of the sentinel node procedure for nodal staging has avoided the morbidity of axillary lymph node dissection in the majority of patients. Several trials demonstrated comparable results with regard to disease-free and overall survival between mastectomy and BCT combined with radiotherapy, and the latter has become the standard of care for early-stage breast cancer. According to national guidelines, 75% of breast cancer patients are suitable for BCT. The main advantage of BCT over mastectomy is preservation of the breast with improved cosmetic outcomes [1-5].

Breast cancer and its treatment have many adverse side-effects, which may be both physical and psychological. Psychological distress is common in the breast cancer population and affects approximately 30% of patients. Fear of disease recurrence, concerns about future health and interruption of life plans often lead to anxiety and depression.

The cosmetic result is also a major determinant of psychological distress. Cosmetic outcome of the breast has a large impact on body image, and studies have shown that women with poor cosmetic outcomes as determined by pronounced breast asymmetry and skin alterations are impaired in their self-esteem, feelings of sexuality and quality of life. Furthermore, these women are more likely to feel stigmatised and have more symptoms of depression. Focusing on the best achievable cosmetic result will lead to a decrease in psychological distress [6-9].

Although BCT is considered the least invasive surgical method for treatment of breast cancer, cosmetic outcomes vary widely. Studies have reported satisfactory cosmetic results in only 60-80% of patients, with cosmetic failure rates up to 40%. Factors determining cosmetic outcome after BCT include the volume of resected breast tissue, the amount of radiotherapy, the site of the tumour in the breast, the type of incision and postoperative complications such as wound infection. Overall, a large volume of resected breast tissue is the major determinant of a poor cosmetic outcome. Regardless of the size of the breast, excision volumes exceeding 85 cm^3 ^result in a 50% rate of cosmetic failures, whereas smaller excision volumes result in only a 22% rate of cosmetic failures. Therefore, surgeons should excise the tumour with only a small volume of surrounding breast tissue [10-15].

As a practical and reasonable guideline during surgery, the aim is to achieve a safe and cosmetically acceptable resection margin of 5-10 mm. It should be noted that the size of the tumour-free resection margin (> 1 mm) is unrelated to local recurrence or overall survival. Higher risks of local recurrence have been shown only with evident involvement of the tumour on the inked resection margins. Therefore, there is no need to excise a tumour with a large volume of adjacent breast tissue. This is also stated by the Dutch national guidelines. Accurate excision leads to a smaller and more precise volume of surrounding breast tissue removal without compromising the minimal tumour-free margin [16-19].

In daily practice, the succes of the removal of palpable breast cancer is based on pre-operative imaging techniques and the experience of the surgeon. The surgeon is guided by intra-operative palpation without objective imaging during the surgery. The primary aim of the procedure is to achieve tumour-free resection margins and to prevent local recurrence; a secondary aim is a satisfactory cosmetic outcome. Avoiding inadequate resection margins and subsequent re-excision results in an unnecessarily wide resection of adjacent healthy breast tissue. Indeed, our recent large retrospective multicentre study demonstrated that during routine breast-conserving surgery, an excessive volume of breast tissue is excised in the majority of patients. The study participants (n = 726) underwent breast-conserving surgery in four hospitals in our region for invasive breast cancer in three consecutive years. The volumes of the excised specimens were calculated using histopathological reports. It was shown that in 33.6% (244/726) of the patients, the excised tissue volume exceeded 85 cm^3^, i.e., deteriorating the cosmetic outcome. In this group, 98.8% (241/244) had presented with an excision that exceeded the optimal resection volume (= the tumour volume plus a 1 cm margin of tumour-free breast tissue). In fact, in 54.9% (134/244) of these patients the tumour stage was T1 and a maximum resection volume of 33.51 cm^3 ^would have been sufficient (optimal resection volume for a tumour size of 2 cm and an added 1 cm margin of healthy breast tissue). Also, in most cases presenting with a tumour-free margin, the malignant lesion was located eccentrically in the excision volume, close to the nearest margin (Figure 1). Remarkably, the rate of focally positive or positive margins was higher for the palpable tumours than for the nonpalpable tumours (22.5% and 17.4%, respectively; P = 0.13) [20]. This might be caused by the lack of three-dimensional orientation with intra-operative visualisation in the excision of palpable tumours.

**Figure 1 F1:**
[figure not shown]
**Specimen with eccentric tumour localisation**.

An easily available and feasible method to improve the amount of healthy breast tissue spared while ensuring tumour-free resection margins is intra-operative ultrasonography (US). US-guided surgery (USS) enables the surgeon to visualise the tumour during excision. Earlier studies have clearly shown the efficacy of USS for nonpalpable tumours. Rahusen et al. reported that USS, in which an experienced radiologist perfomed US, is superior to wire-guided surgery with respect to tumour-free resection margins (89% and 55% of cases, respectively). Snider et al. also showed an excellent rate of tumour-free resection margins using USS (82%) with a smaller volume of healthy breast tissue resection compared to wire-guided surgery (62.2 cm^3 ^and 81.1 cm^3^, respectively) [21-26]. Our retrospective multicentre study showed that USS for nonpalpable invasive breast cancer was more accurate than wire-localisation and Radio Occult Lesion Localisation (ROLL)-guided surgery because it optimised the surgeon's ability to obtain adequate margins (3.7%, 21.3%, and 25% tumour-involved margins, respectively, (P < 0.05). Intra-operative ultrasonography for nonpalpable tumours results in a dramatically lower rate of tumour-involved resection margins than palpation-guided surgery for palpable tumours (3.7% and 22.5%, respectively, (P < 0.05); unpublished data) [27]. To the best of our knowledge, only one study, by Moore et al., has evaluated the use of USS for treatment of palpable invasive ductal breast cancer. One group of patients received USS, and the other group underwent surgery without an imaging technique. The breast tissue spared and margin status were both improved with US [28].

In general, all palpable breast masses are visible by US. Given that the efficacy of USS has already been shown for nonpalpable tumours, we hypothesise that USS will also be useful for palpable tumours with regard to improving the amount of healthy breast tissue spared, cosmetic outcomes and quality of life while still maintaining or even increasing tumour-free resection margins.

